### 3.3. Randomization and Blinding

Participants will be randomly allocated, according to a generated randomization list, to the experimental group (approximately *n* = 50) or the control group (approximately *n* = 50). The randomization list will be generated by a researcher who is not involved in the experiment. The study is designed as double-blinded, meaning that neither the participant nor the intervention conductor will be aware of which group is the experimental group (receiving *Lp299v*) and which is the control group (receiving placebo) until the end of the experiment. Each patient will be assigned a unique code number, which will be used to label all results to maintain blinding.

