## 2. Study Aim and Hypothesis

The primary objective of the trial is to assess the effect of a dietary intervention with probiotic *Lp299v* supplementation on body weight and quality of life in female AIDH patients.

The secondary objective of the trial is to evaluate the effectiveness of individual personalized nutritional counseling on several key parameters among patients diagnosed with Hashimoto’s thyroiditis. The specific focus areas for assessment include food selection and diet quality, body composition, serum anti-TPO, and blood pressure.

The research hypotheses are as follows:-Individual personalized nutrition education aimed at improving food selection and diet quality may enhance nutritional status, anti-TPO parameters in the blood, and the overall quality of life in AIDH patients.-The *Lp299v* strain may augment the impact of the individual nutritional intervention, particularly in terms of improving the quality of life, body weight status, and anti-TPO parameters in the blood.

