### 3.2. Selection of Participants

The selection of the sample for the study will be purposive, taking into account the inclusion and exclusion criteria. Recruitment for the study will be carried out using the snowball method, mainly via social networking sites (i.e., internet websites associated with Hashimoto’s patients). Additionally, collaboration with medical facilities and pharmacies will be established to reach a broader pool of potential participants. The CAWI (Computer-Assisted Web Interview) and PAPI (Paper and Pen Personal Interview) methods will be used for collecting data.

The inclusion criteria will be a medical diagnosis of Hashimoto’s disease based on anti-TPO, anti-TG, or an ultrasound image characteristic of AIDH; thyroid function status (euthyroid, hypothyroidism); female; age in the range of 18-64 years; normal body weight (body mass index BMI 18.50–24.99 kg/m^2^) or excessive body weight (BMI ≥ 25.00 kg/m^2^); and/or low-quality diet (low Pro-Healthy Diet Index (pHDI-10)) [36]. Women with contraindications to a body composition analysis performed using the electrical bioimpedance method (i.e., having a pacemaker) will also be included. However, for these patients, the body composition analysis stage will be skipped.

The exclusion criteria will be thyroid diseases other than AIDH, pregnancy, lactation, diagnosed cancer, and lack of consent to participate in the study. The individual must not take *Lp299v* or medications for weight loss or be diagnosed with celiac disease, Duhring’s disease, or a gluten allergy. The minimum number of subjects (47 for each group) was calculated based on an expected 50% improvement in the overall quality of life after 12 weeks of the intervention in the experimental group, with an assumed 5% significance level and 80% power. The baseline sample size of 100 patients was established to account for potential participant withdrawals.

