### 3.11. Nutrition Education

Nutrition education is planned for 12 weeks, with 6 individual meetings spaced about 2 weeks apart. There will be a total of 6 h of education in the entire program. The form of meetings will be online or in person, depending on the patient’s preferences. At the beginning of the education intervention, the patient will be presented with an interpretation of her eating habits, the nutritional value of her diet, and her nutritional status. A personalized goal (e.g., weight loss in the case of a patient with obesity) that the patient should achieve will also be discussed and set. During the education intervention, the following issues, among others, will be discussed with all participants: nutritional recommendations and essential nutrients (role, sources in food) in Hashimoto’s thyroiditis; factors affecting iron bioavailability; glycemic index and glycemic load—application and importance; weight reduction assumptions; snacking—causes and tips on how to minimize the need to reach for snacks; mindful eating; “Healthy eating plate”—nutritional recommendations for the Polish population presenting the correct proportions of individual product groups in a daily diet [53]; interactions between levothyroxine and food; the importance of microbiota in HT; *Lactobacillus plantarum 299v*—impact on human health based on scientific research (mainly on the immune system, iron, intestinal symptoms, blood pressure); and myths and facts about nutrition in HT. In addition to the above-mentioned topics, participants will be able to receive answers to individual questions/concerns.

All educational materials will be prepared based on the scientific literature and standards by The Polish Society of Dietetics and the National Public Institute—National Institute of Hygiene. Each participant will receive educational materials and a sample menu depending on energy needs to illustrate how meals and portions should look. Throughout the entire study period, participants will have the possibility of consulting with a dietitian, who will also support the introduction of changes in eating habits depending on individual personalized needs.

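### The arm comparisons as described use no baseline covariate, although body weight is primary and BMI classes are mixed; adding baseline BMI and the baseline outcome would gain precision without extra patients

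*Protocol article*

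**What the plan says.** - **Outcome (section 2).** The primary objective concerns the effect of a "dietary intervention with probiotic *Lp299v* supplementation on body weight and quality of life in female AIDH patients".
- **Population (section 3.2).** Women of normal weight are eligible, "or excessive body weight (BMI ≥ 25.00 kg/m^2"). No quota is set for either class.
- **Counselling (section 3.11).** Both arms receive it, and goals are individual: "A personalized goal (e.g., weight loss in the case of a patient with obesity) that the patient should achieve will also be discussed and set".
- **Allocation (section 3.3).** "Participants will be randomly allocated, according to a generated randomization list, to the experimental group" or to control, with about 50 women in each. An independent person makes the list: "The randomization list will be generated by a researcher who is not involved in the experiment". Neither blocks nor strata are mentioned, and neither is ruled out.
- **Analysis (section 3.13).** Multivariate analysis of variance and two-tailed tests compare the arms. Changes from baseline are tested with a dependent-samples t-test or a Mann-Whitney test. No covariate is named for either primary outcome.

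**The concern.** Women who start with excess weight, and in particular those who are given a weight-loss goal, can be expected to lose more weight over 12 weeks than women of normal weight, whichever capsule they take. If the analysis leaves this out, the difference between BMI classes becomes part of the residual scatter. Two things follow. Every realisation of the trial estimates the Lp299v effect on weight less precisely than its data allow. And if one arm happens to receive more women with excess weight, the estimate in that one trial moves, with nothing in the described analysis to pull it back. BMI is already measured at baseline, so using it needs no new data.

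**Working it through.** **Inputs from the protocol article.** N = 100, about 50 per arm (sections 3.2 and 3.3); two-sided 5% level (sections 3.2 and 3.13).

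**Inputs assumed, because the article gives none.** Share p of women with excess weight 30-60%; extra weight loss g in that class 2-4 kg; within-class SD of weight change s = 3 kg.

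**1. Standard error of the arm difference in weight change.** With BMI class in the model, SE = s × √(2/50) = 3 × 0.20 = 0.60 kg. Without it, SE = √(s² + g²p(1−p)) × 0.20:

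| p | g = 2 kg | g = 3 kg | g = 4 kg |
|---|---|---|---|
| 30% | √9.84 × 0.20 = 0.63 | √10.89 × 0.20 = 0.66 | √12.36 × 0.20 = 0.70 |
| 50% | √10.00 × 0.20 = 0.63 | √11.25 × 0.20 = 0.67 | √13.00 × 0.20 = 0.72 |
| 60% | √9.96 × 0.20 = 0.63 | √11.16 × 0.20 = 0.67 | √12.84 × 0.20 = 0.72 |

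The variance rises by g²p(1−p)/s², from 0.84/9 = 9% to 4.00/9 = 44%. That equals a loss of 1 − 1/1.09 to 1 − 1/1.44, or about 9% to 31%, of the information on weight. Simulation of 20,000 trials per scenario gave the same standard errors.

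**2. Chance imbalance in BMI class without strata.** The arm difference in the excess-weight share has SD √(p(1−p) × 2/50), which is 9.2 points at p = 30% and 10.0 points at p = 50%. It lies within about 18-20 points in 95% of trials. The resulting shift in the weight difference is g times the imbalance, so its 95% limit runs from 2 × 0.18 = 0.36 kg to 4 × 0.197 = 0.79 kg. Under simple allocation an imbalance of 20 points or more occurs in about 3-5% of trials.

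**3. Is it bias?** No. In the simulations the unadjusted t-test had an overall type I error of 4.8-5.1% and a mean estimate of about 0 kg. Only in trials with a realised imbalance of 20 points or more did type I error rise, to about 9-24%.

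**4. What adjustment gives.** The model removes the shift, and its price is small. At p = 50% and an imbalance of 20 points, the squared correlation between arm and class is 0.20² = 0.04, so the adjusted SE is 0.60/√(1 − 0.04) = 0.61 kg.

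**5. Do loose arm sizes matter?** The article's 47 per group cannot be reproduced, since neither an SD nor a control value is given. At 80% power it implies a standardized difference of (1.960 + 0.842) × √(2/47) = 0.578. With 100 women, power for that difference is 82.4% at 50:50, 82.0% at 45:55 and 80.8% at 40:60. Fixing the arms at 50:50 also leaves the BMI imbalance unchanged (SD 9-10 points).

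**The case against.** The best case against the point has four parts.

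- **The article is condensed.** List construction and covariates commonly sit in the full protocol or the SAP. This stands for the list: silence and approximate arm sizes do not show simple randomization, and approximate sizes also fit a blocked list with an incomplete last block. It stands less well for the analysis, because section 3.13 does name its tests, and those named do not use baseline BMI. It does not exclude such a factor either.
- **Randomization already covers chance imbalance.** This stands. The p-value allows for it, and step 3 confirms that. What remains is the avoidable loss of precision.
- **Changes from baseline already use baseline weight.** A change score removes differences in starting level. It does not remove a difference between BMI classes in how much weight is lost, and that is what step 1 measures.
- **The link between goal and BMI class rests on one example.** The example concerns obesity, which section 3.8 sets at 30.00 kg/m² or more, and section 3.11 discusses weight reduction with all participants. This stands as a caution on size. If only women with obesity lose more and they are 20% of the sample (assumption), the unadjusted SE is √(9 + 4 × 0.16) × 0.20 = 0.62 kg to √(9 + 16 × 0.16) × 0.20 = 0.68 kg. The gain shrinks but does not vanish.

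**Conclusion.** The point holds as a free improvement to the analysis, not as an error that threatens validity. As described, the comparison leaves out a plausible predictor of a primary outcome that is already measured. Under the stated assumptions the SE for weight is about 0.63-0.72 kg where about 0.60 kg is attainable. The BMI mix, the gap in weight loss and the SD are all assumed, so the kilogram figures are illustrative. For quality of life the article gives nothing from which to size the gain.

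A reader might infer three stronger things that the documents do not support:

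- **That an imbalance in BMI could not be distinguished from an Lp299v effect.** BMI is recorded, so the imbalance can be seen and adjusted for, and on average over randomizations it is zero.
- **That the list is unrestricted.** The article does not say so.
- **That approximate arm sizes endanger "The minimum number of subjects (47 for each group").** Under simple allocation the smaller arm would fall below 47 with probability 0.48, but even 40:60 costs under 2 points of power, and arm sizes have no bearing on BMI imbalance.

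**What to change.** In section 3.13, state that 12-week body weight and 12-week quality of life are each compared between the arms in a linear model with terms for arm, the baseline value of the outcome, and baseline BMI. BMI may enter as class (below 25.00 / 25.00 kg/m² or more) or as a continuous value. For the weight model, continuous baseline weight can serve as both the baseline value and the body-size term. Choose one form in advance. The continuous form does not depend on whether the weight-loss goal starts at overweight or at obesity. If the SAP already contains such a model, one sentence in section 3.13 settles the matter.

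The cost is one or two degrees of freedom and a short text change, made before unblinding. No extra patients or measurements are needed, and the change remains possible after allocation has begun.

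Optionally, if the list has not yet been generated, the independent researcher can stratify it by BMI class in randomly permuted blocks of varying size. BMI class must then be known at allocation, which eligibility already requires. If the list is already blocked or stratified, section 3.3 should say so, and the stratum should appear in the model.

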### 3.4. Course of Intervention

The 12-week intervention will involve individual nutrition education for patients with Hashimoto’s thyroiditis conducted in two groups. One group will additionally receive the *Lp299v* strain (NE + *Lp299v* group), and the other will receive a placebo (NE + P group). Before the start of education, an assessment of dietary habits will be performed using a three-day food record questionnaire. Additionally, validated tools will be used to assess (1) the dietary habits and nutritional beliefs (FFQ-6 and KomPAN^®^ questionnaire [36,37]); (2) the quality of life with thyroid diseases (ThyPROpl) [38]; (3) physical activity level (Polish version of IPAQ questionnaire) [39]. Anthropometric measurements (body weight and height, waist and hip circumferences), body composition, peripheral arterial pressure, and anti-TPO blood concentration measurements will also be performed. All parameters will be measured twice: at baseline and after 12 weeks of the intervention to evaluate changes and (if possible) compare the measurements to reference values. A diagram of the study is presented below (Figure 1).

### 3.5. Nutrient Intake and Diet Quality

The energy and nutrient intake will be assessed using the three-day food record method recommended by The Polish Society of Dietetics and the National Consultant of Family Medicine [40]. Participants will be asked to record everything that they eat and drink in household measures or grams on three non-consecutive days (two typical and one non-typical). Before completing the food record, patients will be instructed on how to properly fill out the questionnaire and will receive an example of a completed form to illustrate the task. After returning the completed food record, the average energy and nutrient intake will be calculated for each patient using a special computer application, “DietetykPro^®^” (Poland), with the Polish nutrient database for food products and dishes [41]. In the absence of a recorded product, the United States Department of Agriculture (USDA) nutrient database [42] will be utilized, or the most similar product will be chosen to calculate the nutrient content. Diet adequacy will be assessed by comparing the average intake of nutrients (macronutrients, minerals, and vitamins) with the Polish nutritional standards and recommendations [43]. Energy intake will be compared to the individual’s total energy needs, estimated by multiplying the individual’s basal metabolic rate (calculated with Mifflin St Jeor equations [44]) by the physical activity factor (physical activity level (PAL): 1.4 to 1.69—sedentary or light-activity lifestyle; 1.7 to 1.99 active or moderately active lifestyle; 2.00–2.40 highly physically active lifestyle) of the patient [45].

To assess the consumption frequency of selected food products and eating habits, the Polish-validated Food Frequency Questionnaire (FFQ-6) will be used. The questionnaire covers 62 different food products. Participants must choose one of the six categories indicating the frequency of food consumption over the past 12 months: (1) never or almost never, (2) once a month or less, (3) several times a month, (4) several times a week, (5) daily, (6) several times a day. The questionnaire also includes socio-demographic questions necessary to characterize the group [37].

To assess the overall quality of the diet, the following Polish-validated tools will be used: the Pro-Health Diet Index (pHDI-10) and the non-Healthy-Diet Index (nHDI-14) [36]. The first one includes ten food items: whole-grain bread/rolls, coarse-grounded groats, milk, fermented milk beverages, fresh cheese curd products, white meat, fish, legume-based foods, fruit, and vegetables. The latter includes fourteen food items: white bread and bakery products, white rice and fine-ground groats, fast foods, fried foods, butter, lard, cheese, cured meat/smoked sausages/hot dogs, red meat, sweets, tinned meats, sweetened beverages, energy drinks, and alcohol. Based on the answers provided by each individual, the total points are recalculated to a range of 0%–100% according to the questionnaire’s manual. The index value reflects the intensity of beneficial or harmful characteristics for health. For example, pHDI-10 scores ranging from 0 to 33 indicate low diet quality [36].

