### 3.7. Quality of Life

The quality of life of the participants will be assessed using the Quality of Life Questionnaire for Patients with Thyroid Diseases (ThyPROpl).

ThyPROpl is a thyroid-specific questionnaire validated for the Polish population by Sawicka-Gutaj et al. [38]. The questionnaire comprises 85 questions grouped into 13 scales measuring aspects of quality of life relevant to thyroid patients. The 13-point scale includes questions on (1) symptoms, (2) feeling tired, (3) energy, (4) memory and concentration, (5) nervousness and tension, (6) mental well-being, (7) problems with coping or mood swings, (8) relationships with other people, (9) daily activities, (10) sex life, (11) the impact of the disease or its treatment on appearance, (12) the intensity of the impact of the disease on the subject in general. All quality-of-life questions will cover the last 4 weeks prior to the survey. The respondents must choose 1 of 5 answer categories: (1) not at all, (2) a little, (3) average, (4) quite a lot, (5) very much. In the question regarding difficulties in performing duties at work, the authors added an additional category—“I do not work” [38]. The score ranges from 0 to 100, with higher scores indicating a poorer quality of life.

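### The FFQ-6 asks about the past 12 months but is repeated after 12 weeks, so 77% of its follow-up recall window precedes the intervention and change in food frequency is understated

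*Protocol article*

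**What the plan says.** Section 3.5 gives the FFQ-6 the task of recording how often 62 products are eaten, and fixes its reference period: "Participants must choose one of the six categories indicating the frequency of food consumption over the past 12 months". The categories run from 1 (never or almost never) to 6 (several times a day).

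Section 3.4 names the FFQ-6 among the tools and then states: "All parameters will be measured twice: at baseline and after 12 weeks of the intervention to evaluate changes". Nothing in the article exempts the FFQ-6 from the second measurement or gives it a shorter window at follow-up.

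Section 3.11 sets the length and pace of the education: "Nutrition education is planned for 12 weeks, with 6 individual meetings spaced about 2 weeks apart". Section 2 makes its effect on diet part of the secondary objective: "The specific focus areas for assessment include food selection and diet quality, body composition, serum anti-TPO, and blood pressure".

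Two other instruments have different time frames. For nutrients, section 3.5 says: "The energy and nutrient intake will be assessed using the three-day food record method". For quality of life, section 3.7 says: "All quality-of-life questions will cover the last 4 weeks prior to the survey". Section 3.5 describes the diet indices pHDI-10 and nHDI-14 without any recall period.

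**The concern.** A questionnaire that looks back 12 months describes usual diet. Used 12 weeks into an intervention, it mixes a short period of the new diet with a much longer period of the old one, and the baseline answer describes only the old one. The difference between the two visits is then pulled toward zero for anyone who follows the instruction. A woman who ignores the instruction and reports her recent diet escapes the dilution, but her effective window is unknown and may differ from that of other women and between her own two visits.

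Both arms receive the education, so the objective of judging the counselling rests on change within patients from before to after. That is the quantity being shrunk. A small or absent FFQ-6 change could be read as counselling that failed to alter food choice, when the form was mostly asking about the months before it began. By contrast, the 4-week window of the quality-of-life questionnaire falls wholly inside the intervention at week 12.

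**Working it through.** The plan gives no figure of its own on this point, so there is none to reproduce.

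**Inputs from the article.** Recall window: 12 months, taken as 52 weeks (section 3.5). Follow-up: week 12 (section 3.4). Education: six meetings about two weeks apart (section 3.11).

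**Step 1: overlap of the windows.**
- Share of the follow-up window before the intervention: (52 − 12)/52 = 40/52 = 76.9%.
- Share during the intervention: 12/52 = 23.1%.
- In days, 84/365.25 = 23.0%, so the choice of unit does not matter.

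**Step 2: effect on mean frequency.** Assume that the woman averages over the stated window, and that she changes from frequency a to frequency b in full on day 1. The reported mean is (40a + 12b)/52. The visible change is 12(b − a)/52, which is 23.1% of the true change for any a and b.
- Example: once a week to 7 times a week gives (40×1 + 12×7)/52 = 124/52 = 2.4 per week. The visible rise is 1.4 of a true 6.
- A gradual change shows less. With a steady ramp over the 12 weeks (my assumption), the average new diet is half-way to b, so 6/52 = 11.5% is visible.

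**Step 3: effect on the six categories.** The article attaches no numbers to its categories, so the frequencies here are assumptions.
- Several times a month (category 3, taken as 3 in 30 days, or 0.7 per week) to daily (category 5): (40×0.7 + 12×7)/52 = 112/52 = 2.2 per week. That is category 4, so one step is recorded where two occurred.
- Several times a week (category 4, taken as 3 per week) to daily (category 5): (40×3 + 12×7)/52 = 204/52 = 3.9 per week. That is still category 4, so no change is recorded.

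The loss is half of the shift in the first example and all of it in the second.

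**Step 4: with a window of 12 weeks or less at follow-up.** The share before the intervention falls from 76.9% to 0%, and the averaged report can reflect up to 100% of the change.

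**The case against.** The strongest case against the point is about its reach and size.

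- **Other dietary measures.** A reader might infer that all dietary change in this trial is diluted. The article does not support that. Nutrient intake comes from the food record, which captures current diet, and section 3.5 assigns overall diet quality to pHDI-10 and nHDI-14, whose recall period is not given. Section 3.13 mentions diet quality scores as an example of the variables tested for change and does not name FFQ-6 frequencies; its list is only illustrative, so that does not exclude them. This objection stands and limits the point to the FFQ-6.
- **A fixed attenuation.** A reader might also conclude that the FFQ-6 cannot show a 12-week change, or that it always loses 77% of one. Neither holds. The first category example still shows a one-step shift, and 77% applies to a mean frequency under full averaging, not to ordinal categories. This stands too.
- **Recent-diet answers.** Respondents may answer mainly from recent weeks. Then the loss is smaller, but the form is not being used as described.
- **Primary outcomes and group comparison.** Body weight and quality of life are unaffected. Both arms complete the same form, so the window mismatch creates no false difference between them. That is correct, and it keeps the point at the level of a secondary measure.
- **A condensed article.** Follow-up wording might sit in a fuller protocol. But this article states the window, the timing and the purpose, and as stated they do not fit together.

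**Conclusion.** The mismatch is real on the printed text. At week 12, 77% of the FFQ-6 recall window precedes the intervention, and answers given as instructed understate change in food frequency. The direction of the bias is toward zero.

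The 77% follows from the stated window and timing, and assumes only that the FFQ-6 is among the parameters measured twice, which nothing in the article contradicts. The 23% visible change also assumes full averaging and a change made on day 1. For category shifts no single figure holds.

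The consequence is limited to what the trial can say from the FFQ-6 about food selection, one part of the secondary objective. It is worth correcting because it is cheap to do in advance, and answers collected with the wrong window cannot be repaired afterwards.

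**What to change.** Choose one of two routes and state it in section 3.5.

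1. **Change the window.** Set the FFQ-6 reference period to no more than 12 weeks, with the same length at baseline and follow-up. This alters one instruction line. The cost is a departure from the validated 12-month period, to be declared as a limitation. A short window also no longer averages over the seasons, so the before-after change may carry a seasonal component, although the comparison between arms should not if both recruit over the same months.
2. **Restrict the use.** Keep the 12-month form, use it only to describe baseline diet, and exempt it explicitly from the repeat measurement in section 3.4. Draw no conclusion on dietary change from it, and rely on the three-day food record for change in intake. This costs nothing to run, but gives up a before-after measure of habitual frequency for the 62 products, which three recorded days do not replace.

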### 3.6. Selected Lifestyle Factors

The participants’ levels of physical activity will be assessed using the International Physical Activity Questionnaire (IPAQ), validated by Biernat et al. [39]. The Polish version quantifies physical activity in metabolic equivalent of task (MET)-min/week units, which allows the respondents to be easily classified into one of three categories of activity: insufficient (below 600), sufficient (600–3000), or high (above 3000 MET-min/week). The questionnaire comprises two parts: The first includes six brief questions (with Yes/No responses), designed to verify whether the preceding seven days were representative of the participant’s typical level of physical activity. In the second part, participants answer seven questions related to physical activities at both intense and moderate levels, as well as all walking and sitting [39].

Self-reported data on health status, sleep duration, and smoking status will be collected using the KomPAN questionnaire [36]. Additionally, all participants will be queried about ongoing medical care, medications, and dietary supplements and herbs, along with an assessment of their stress levels.

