### 3.13. Statistical Analyses

All statistical analyses will be conducted using Statistica 13.1 PL (StatSoft Inc., Tulsa, OK, USA; StatSoft, Krakow, Poland). Categorical variables will be presented as a sample percentage (%). Continuous variables will be presented as means with 95% confidence intervals (95%CIs) for variables with a normal distribution or medians with an interquartile range (IQR) for variables with a non-normal distribution. To assess the impact of the nutritional intervention with probiotic supplementation and verify the differences between the experimental and control groups, multivariate analysis of variance and two-tailed tests will be applied. The normality of the variable distribution will be assessed using the Shapiro–Wilk test before statistical analysis. For continuous variables, e.g., diet quality scores, scores of quality of life, markers of adiposity, metabolic parameters, and changes after 12 weeks of education relative to baseline, will be assessed using a *t*-test for dependent samples for normally distributed variables or a Mann–Whitney test for variables without a normal distribution. Differences in categorical variables will be examined using the Pearson chi-squared test. *p* < 0.05 will be considered statistically significant.

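### FFQ-6 food frequencies are ordered, but the only test named for categorical variables ignores order; if it is used to compare the arms item by item, about half of a rank test's power is lost at odds ratios of 1.5 to 2

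*Protocol article*

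**What the plan says.** Section 3.5 of the protocol article describes FFQ-6: "The questionnaire covers 62 different food products". The response format is "Participants must choose one of the six categories indicating the frequency of food consumption", with a recall period of 12 months. The six answers run in order, from practically never up to more than once a day.

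Section 3.13 gives the rule for such data: "Differences in categorical variables will be examined using the Pearson chi-squared test". It names no trend or ordinal method for categorical variables. Two other methods appear in the same paragraph. For the effect of the intervention and the group differences, "multivariate analysis of variance and two-tailed tests will be applied". In a sentence that opens with continuous variables and covers change from baseline, it names "a Mann–Whitney test for variables without a normal distribution". That sentence's examples include diet quality scores but not FFQ-6 items.

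Section 2 places food choice under the secondary objective, on counseling: "The specific focus areas for assessment include food selection and diet quality".

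Section 3.6 has a second ordered classification. IPAQ respondents are "easily classified into one of three categories of activity", but the same instrument also yields MET-min/week.

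**The concern.** On a plain reading, an item answered in categories falls under the chi-squared sentence. For two arms and six categories, Pearson chi-squared tests for any difference in pattern, spread over 5 degrees of freedom. The question in a nutrition trial is narrower: is a food eaten more often, or less often, in one arm? A test that uses the order concentrates on that single direction.

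Two things are at stake. A one-directional shift in food frequency is harder to detect than it need be with the same data. And a significant result says only that the distributions differ. The reader must inspect the percentages to see which way, and gets no effect estimate or interval.

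**Working it through.** **Inputs from the article.** Six ordered categories (3.5); Pearson chi-squared for categorical variables and significance at p < 0.05 (3.13); a minimum of 47 women per group (3.2) and about 50 per group allocated (3.3). The article states no power for food selection, so there is no figure to reproduce. The 47 was set for quality of life and is used here only as the available sample size.

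**Assumed, because the article does not give them.** The size of the shift (odds ratios 1 to 4 under proportional odds) and the baseline distribution over the six categories (four shapes: uniform, bell-shaped, skewed low, skewed high).

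**Step 1: a worked case.** Take a control distribution p = (0.15, 0.20, 0.25, 0.25, 0.10, 0.05), with cumulative values 0.15, 0.35, 0.60, 0.85, 0.95. Divide each cumulative odds by 2. For example, 0.15/0.85 = 0.1765; halved it is 0.0882; 0.0882/1.0882 = 0.0811. The shifted cumulative values are 0.0811, 0.2121, 0.4286, 0.7391, 0.9048, so q = (0.0811, 0.1310, 0.2165, 0.3106, 0.1656, 0.0952).

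For equal arms of size n, the noncentrality of Pearson chi-squared is λ = n Σ (p − q)²/(p + q). The six terms are 0.0205, 0.0144, 0.0024, 0.0066, 0.0162 and 0.0141, which sum to 0.0742. With n = 47, λ = 3.49. The rank test has practically the same noncentrality (3.49), but on 1 degree of freedom. The 5% critical values are 11.07 (5 df) and 3.84 (1 df), so power is:

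- Pearson chi-squared, 5 df: 25.6%
- Rank test, 1 df: 46.3%

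The relative loss is 1 − 25.6/46.3 = 45%. At odds ratio 3 the same steps give λ = 8.37 (8.36 for the rank test) and power of 58.7% against 82.4%, a loss of 29%. The signal is the same in both tests; the loss comes from spreading it over 5 degrees of freedom.

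**Step 2: simulation.** 20,000 trials per setting, two-sided 5%, Pearson chi-squared against the tie-corrected Mann–Whitney test. Ranges are over the four baseline shapes.

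| Odds ratio | 47 per arm: chi-squared vs rank | 50 per arm: chi-squared vs rank | Relative loss, both sizes |
|---|---|---|---|
| 1.5 | 10–11% vs 19–20% | 10–11% vs 20–21% | 47–50% |
| 2 | 22–25% vs 45–47% | 24–27% vs 48–49% | 44–51% |
| 2.5 | 40–43% vs 68–69% | 43–46% vs 71–73% | 37–41% |
| 3 | 56–59% vs 83–84% | 59–63% vs 85–87% | 27–33% |
| 4 | 80–82% vs 96% | 83–85% vs 97% | 12–16% |

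With no true difference, both tests reject in about 4–5% of trials. A linear trend test is within about 3 percentage points of the rank test.

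**Step 3: check without a baseline shape.** With equal noncentrality, power of 50% on 1 df (λ = 3.84) becomes 28% on 5 df, and 80% (λ = 7.85) becomes 56%. The relative losses are 44% and 31%, in line with the table.

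**The case against.** The strongest objection is that section 3.13 never says FFQ-6 items go to chi-squared. The codes 1 to 6 could be scored, and the paragraph already names a rank test. This stands in part: a reader might infer that the trial will certainly lose half its power on food choice, and the text does not support that. But the Mann–Whitney sentence is introduced for continuous variables, section 3.5 itself calls the answers categories, and no ordered method is named for categorical data.

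Second, food selection belongs to a secondary objective about counseling, which both arms receive. The probiotic hypothesis stresses quality of life, body weight and anti-TPO. This stands and limits the importance. So does the recall window: FFQ-6 asks about 12 months, while follow-up is at 12 weeks, so most of the window at the second measurement predates the intervention. Any true between-arm shift may be small, and a better test does not cure that.

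Third, the main dietary outcomes are untouched. pHDI-10 and nHDI-14 are scores that 3.13 treats as continuous, and nutrient intakes from the food record are numeric. This also stands. Extending the point to IPAQ adds little, because MET-min/week is available.

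Fourth, a condensed article may leave item-level analysis to a plan not shown here. That would answer a complaint about missing detail. Here, however, the article states a method for categorical variables, without exception.

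A reader might also infer that chi-squared is invalid here, that it hides direction altogether, or that real shifts will usually be missed. None of these holds in general. Type I error is close to 5%; categorical variables are to be presented as percentages, so direction can be read off; and at odds ratio 3 chi-squared still has 56–63% power.

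**Conclusion.** The concern holds in conditional form. If FFQ-6 items are compared between arms by the rule in 3.13 for categorical variables, the test discards the order of the answers. With 47 to 50 women per arm, that costs about half the power of a rank test at odds ratios 1.5 to 2, about 30% at 3, and 12–16% at 4. The loss is near one half only where the rank test itself has about 19–49% power.

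These figures rest on assumed proportional-odds shifts and assumed baseline distributions; the article supplies neither. This is a matter of efficiency and interpretability in a secondary, item-level outcome. It does not threaten the primary objective. It is still worth correcting, because a stated method can be replaced by a better one using data already planned.

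**What to change.** In section 3.13, limit Pearson chi-squared to unordered categories and add a sentence such as: FFQ-6 item frequencies at week 12 will be compared between arms with a proportional-odds model containing arm and baseline category, and reported as a common odds ratio with a 95% CI. A rank or trend test on the ordered categories is an acceptable simpler choice, provided that a directional estimate with a 95% CI accompanies it. If IPAQ is compared, use MET-min/week and treat the three classes as ordered where they are reported.

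The cost is one or two sentences, with no new data, visits or participants. The downside is somewhat less sensitivity to differences without a direction, such as one arm having more answers at both extremes. The stated hypotheses, which are about improvement, do not predict such a pattern.
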